### Metabolomics substudy

During SAM, metabolic processes are altered in response to a starved environment and may plausibly contribute to long-term clinical outcomes. Previous studies suggest that amino acid turnover, lipid metabolism, oxidative stress and other metabolic pathways are disrupted in SAM and may be associated with disease state and clinical outcome^26 44 45^; however, little is known about how the metabolic phenotype responds to nutritional therapy. It is hypothesised that disturbed gut microbiota composition and function may drive microbial metabolic dysregulation in addition to host-derived dysregulation. Of particular interest are differences in the metabolic phenotype between oedematous and non-oedematous SAM. The ‘reductive adaptation’ seen in non-oedematous SAM (utilisation of fat and muscle stores) is disrupted in oedematous SAM, which may contribute to differences in clinical outcomes. Specifically, protein turnover, inflammation, oxidative stress and bile acid metabolism are disrupted in oedematous-SAM, which may contribute to comorbidities including diarrhoea, steatosis and enteropathy.^46 47^

We hypothesise that (i) a unique plasma and urine metabolic phenotype exists in oedematous compared with non-oedematous SAM during hospitalisation, which is independently associated with morbidity, mortality and nutritional recovery; (ii) the metabolic phenotype is partially restored to a healthy state with nutritional rehabilitation but reverts to a disturbed state during follow-up, which predicts morbidity, mortality and relapse; and (iii) both host-derived and gut microbial-driven metabolic dysregulation underlie clinical outcomes.

Using stored urine and plasma samples collected during hospitalisation, a cross-sectional investigation will determine differences in the metabolic phenotype between children with oedematous SAM, non-oedematous SAM and well-nourished controls. Urine and plasma metabolic phenotypes will be compared between groups at discharge and 12, 24 and 48 weeks post discharge. Briefly, global untargeted metabolomic phenotyping will be performed via ^1^H nuclear magnetic resonance (NMR) spectroscopy using a 700 MHz Bruker NMR spectrometer to identify metabolic signatures of SAM. Targeted analysis via ultra-performance liquid chromatography-mass spectrometry will be performed to examine specific pathways of interest, including tryptophan and bile acid metabolism.

### Immunology substudy

Bacterial infections are common among children hospitalised for SAM^23 48–50^ and mortality is driven by a range of species,^48 50–53^ consistent with generalised defects in innate antibacterial defence. Increased infectious morbidity and mortality persist after discharge from hospital,^10 17 54^ suggesting that restoration of antibacterial immune responses may lag behind nutritional rehabilitation. A recent randomised trial in children with SAM confirmed that deaths following hospitalisation were predominantly due to bacterial infections but were not prevented by daily co-trimoxazole prophylaxis.^17^ Collectively, these observations highlight that children remain vulnerable to infection despite current treatment approaches; targeting persistent immune dysfunction could plausibly reduce infectious mortality after discharge.^24^

Multiple innate and adaptive immune mediators are dysregulated in malnutrition.^24 27 55^ However, few studies have assessed cellular immune function in malnourished children; most existing studies were undertaken decades ago on small cross-sectional cohorts without the benefit of recent advances in immunology techniques.^27^ Immune dysfunction in SAM likely reflects both *intrinsic* defects, whereby immune cells lack capacity to adequately respond to infection, and *extrinsic* defects, where cells have intact antibacterial capacity but are chronically modulated by the systemic pro-inflammatory environment which characterises SAM (ie, heightened pro-inflammatory cytokines^44^ and circulating bacterial antigens^23 56 57^). Systemic inflammation is directly associated with mortality in SAM^23^ and driven by multiple comorbidities, including bacterial translocation from the damaged gut into the blood, subclinical infections and metabolic dysregulation.^44 58 59^ The implications of innate immune cell dysfunction for subsequent acquisition of infections and infectious mortality have not been investigated.

We hypothesise that (i) antibacterial functions of innate immune cells are compromised in SAM due to a combination of intrinsic and extrinsic defects; (ii) innate immune cell function is independently associated with infectious morbidity and mortality during hospitalisation for SAM; and (iii) nutritional rehabilitation only partly restores innate immune cell function, leading to an ongoing risk of bacterial infections post discharge.

Using blood samples collected at baseline, discharge and 12, 24 and 48 weeks post discharge, the longitudinal relationship between circulating innate immune cell function and bacterial infections will be assessed. The intrinsic phagocytic capacity, secreted cytokine response and maturation state of innate immune cells after culture with bacterial antigens will be assessed. Plasma concentrations of endotoxin and pro-inflammatory mediators will be quantified at each time point and the degree to which these extrinsic factors influence innate immune cell antibacterial function will be assessed via plasma co-culture with innate immune cells from healthy donors. Bacterial infections during hospitalisation will be diagnosed using clinical criteria and blood culture, stool culture and urinalysis where available.

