## Study procedures

Study procedures are outlined in table 2.

**Table 2 T2:** Summary of procedures in observational cohort

Assessment	Hospitalisation		Post discharge*				
	Baseline†	Discharge‡	2 weeks	4 weeks	12 weeks	24 weeks	48 weeks
Caregiver informed consent to join observational cohort	x						
Summary checklist	x						
Locator information§	x						
Acute admission information	x						
Baseline data	x						
Daily clinical review¶	Daily during hospitalisation						
Blood collection**	x	x			x	x	x
HIV testing††	x						
CD4 count and viral load (HIV-infected children only)	x				x	x	x
Full blood count‡‡	x	x			x	x	x
Anthropometry	x	x	x	x	x	x	x
Skinfold thickness§§		x	x	x	x	x	x
Body composition¶¶	x	x	x	x	x	x	x
Discharge data collection		x					
Daily morbidity diary			Daily during follow-up period by caregivers				
Follow-up clinic: history, examination, morbidity and mortality data			x	x	x	x	x

*Windows will be created around these post-discharge time-points to maximize follow-up for caregivers who miss visits or are unavailable, as follows: 2 weeks (optimal window from 1 week to 2 weeks + 6 days; allowable window up to 2 weeks + 6 days); 4 weeks (optimal window 3-5 weeks, allowable window up to 9 weeks + 6 days); 12 weeks (optimal window 10-14 weeks, allowable window up to 19 weeks + 6 days); 24 weeks (optimal window 20-28 weeks, allowable window up to 43 weeks + 6 days); 48 weeks (optimal window 44-52 weeks, allowable window up to 71 weeks + 6 days). †Children will be enrolled as soon as possible after hospitalisation and will undergo baseline investigations as soon as possible after enrolment. This is to provide a window of opportunity to time collection of research specimens with clinical specimens, and to ensure that the child is clinically stable before undertaking research investigations.

‡The discharge procedures will be undertaken on the day of discharge or as close as possible to that date.

§Locator information will be updated at subsequent visits if caregivers have moved or changed contact details.

¶A clinical review will be undertaken every day between admission and discharge by the study clinician.

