### Daily procedures

Routine inpatient management is undertaken by ward clinical teams according to local hospital protocols, which are based on WHO guidelines.^2^
^33^ In addition, the HOPE-SAM study clinician at each hospital site collects daily data until discharge on clinical parameters (including daily examination), resolution of acute infections, nutritional recovery (loss of oedema, restoration of appetite, weight gain) and treatment/nutritional supplements received; this will allow us to evaluate differences in management between countries. Children with HIV-SAM who are ART-naive start ART according to national guidelines, which are based on WHO recommendations.^2 34^

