## Study outcomes and risk factors

The main study outcomes are clinical (mortality, morbidity and relapse of malnutrition) and nutritional (weight, height, MUAC, leg length, head circumference, mid-thigh circumference, skin-fold thickness and body composition by bioimpedance vector analysis) assessed over 48 weeks of follow-up. Mortality is assessed in hospital by daily physician review and, post discharge, through study visits and by telephone where possible for children who are lost to follow-up. Morbidity during hospitalisation is assessed through daily clinical assessments and available hospital laboratory tests. Morbidity after discharge is assessed, first, using daily morbidity diaries, in which caregivers record episodes of illness (lethargy interfering with feeding; respiratory distress; diarrhoea; oedema and fever); second, from caregiver recall and review of handheld medical records at each follow-up visit; and, third, from data collected during hospitalisation for children who are readmitted during the follow-up period. Time-to-recovery from malnutrition will be evaluated during hospitalisation; relapse of malnutrition during follow-up will be categorised as moderate acute malnutrition, uncomplicated SAM and complicated SAM, according to WHO definitions. Nutritional outcomes will be expressed both as continuous variables (attained Z-score and change in Z-score between visits), and as categorical variables (moderate wasting, WHZ<–2; severe wasting, WHZ<–3; stunting, HAZ<–2; severe stunting, HAZ<–3; underweight, WAZ <–2; and microcephaly, head circumference-for-age <–2).

Risk factors will be evaluated at baseline, hospital discharge and over the period of follow-up for associations with clinical and nutritional outcomes. In addition to baseline clinical and demographic factors, the following laboratory parameters will be evaluated: haemoglobin, serum albumin, C reactive protein (CRP), CD4 count and HIV viral load (for HIV-positive children). Haemoglobin, CD4 and HIV-viral load will be measured in real time and the results reviewed during follow-up clinics.

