### Observational cohort

The primary comparison will be the clinical and nutritional outcomes of children with HIV-SAM compared with HIV-negative children with SAM. We will review all deaths and adjudicate clinical diagnoses and causes of death to ensure robust and consistent data across sites. We will compare each participant’s clinical management to WHO guidelines to identify any contributory factors in hospital care. Factors associated with outcomes during hospitalisation (eg, mortality, nutritional recovery) will be determined for each group (HIV-SAM and HIV-negative children with SAM) using multivariable analysis (Cox models for time-to-event data, linear models for continuous outcomes). Factors associated with outcomes over 48 weeks post discharge (hospital readmission, morbidity and mortality, relapse, anthropometry, body composition and response to ART) will be determined for each group (HIV-SAM and HIV-negative children with SAM) using multivariable analysis (Cox models for time-to-event data, linear models for continuous outcomes). HIV-positive children with SAM and HIV-negative children with SAM will be included in one model together with the risk factors, and interaction tests will be used to investigate whether associations between risk factors and outcomes differ between the two groups of children. We will evaluate the ability of MUAC at discharge to predict long-term outcomes using receiver-operator-characteristic (ROC) analysis, in the whole cohort and within the subgroups of HIV-SAM and HIV-negative children with SAM. We will then evaluate whether addition of other variables improves the predictive capacity of MUAC (using WHO criteria in those >6 months, and published data for children <6 months^62^) for each group, including body composition, haemoglobin, albumin and CRP, plus CD4%, viral load and timing of ART initiation (HIV-SAM only). We will construct multivariable models and compare them with MUAC alone using the net-reclassification index.

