### Immunology substudy

Integrated profiles of innate immune cell function will be generated for each child using principal components analysis followed by hierarchical clustering.^65 66^ This data -reduction method identifies whether absolute levels of specific markers or relative differences between markers differentiate children into groups. The resulting innate immune profiles will be compared between HIV-SAM, HIV-negative children with SAM and well-nourished groups using univariable tests and multivariable analysis of variance of the principal components.

To address the relationship between immune function and infections, regression analyses will determine whether baseline innate immune profiles (or the individual parameters defining them) are associated with the infectious morbidity or mortality during hospitalisation, using logistic models for binary outcomes and linear models for duration. Key clinical characteristics, including age, sex, oedema and baseline WHZ, will be added to models to investigate their confounding effects. Multivariable stacked regression methods will be used to compare the impact of different factors on severe bacterial infections based on heterogeneity tests.

To determine whether treatment for SAM restores innate immune cell antibacterial function, mixed effects regression models will compare longitudinal changes in individual immune parameters, and the principal components calculated from the weights identified at baseline (which include well-nourished controls). Similarities and differences in longitudinal immune profiles will be compared between groups using non-metric multidimensional scaling.^65 67 68^ This approach will group children according to their composite innate immune function, allowing the duration and variability of immune restoration to be evaluated over the course of nutritional rehabilitation. Binary logistic regression will determine whether innate immune profiles at discharge are associated with morbidity or mortality during follow-up.

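### In-hospital bacterial infection relies partly on cultures and urinalysis done only where available, so unequal testing may bias its associations with immune profile and HIV

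*Protocol article*

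**What the plan says.** The Immunology substudy text under Substudies defines the infection outcome: "Bacterial infections during hospitalisation will be diagnosed using clinical criteria and blood culture, stool culture and urinalysis where available". Study outcomes and risk factors takes a similar line for the whole cohort: "Morbidity during hospitalisation is assessed through daily clinical assessments and available hospital laboratory tests".

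One component is uniform. The footnotes to Table 2 say: "A clinical review will be undertaken every day between admission and discharge by the study clinician". The other is left to usual care. Under Daily procedures, "Routine inpatient management is undertaken by ward clinical teams according to local hospital protocols", at three hospitals in two countries. Tables 2 and 3 schedule research blood, HIV tests, blood counts and substudy stool and urine, but no diagnostic blood culture, stool culture or urinalysis.

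The Immunology substudy part of Analysis then uses the outcome. Regressions ask whether baseline innate immune profiles "are associated with the infectious morbidity or mortality during hospitalisation, using logistic models for binary outcomes and linear models for duration". On adjustment it says: "Key clinical characteristics, including age, sex, oedema and baseline WHZ, will be added to models to investigate their confounding effects". It adds: "Multivariable stacked regression methods will be used to compare the impact of different factors on severe bacterial infections based on heterogeneity tests". Neither hospital nor whether a test was done is named, although the list is worded as open. The observational cohort analysis makes HIV-positive v HIV-negative children the primary comparison for clinical outcomes, which include morbidity. It also states a safeguard: "We will review all deaths and adjudicate clinical diagnoses and causes of death to ensure robust and consistent data across sites".

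**The concern.** A child who was never cultured cannot contribute a positive culture. If tests add cases to those found clinically, the group tested more often will show more infection at the same true rate. Ward teams may well culture children who look sicker or more inflamed, and practice may differ by HIV status and by hospital. That is an assumption, but a plausible one: the article itself expects to compare management between countries. Severity and inflammation are also close to the exposures under study.

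Two analyses are exposed. The first is the immunology substudy's central hypothesis, that innate immune function is independently associated with infectious morbidity in hospital. The second is the infection part of in-hospital morbidity in the HIV comparison. Age, sex, oedema and WHZ would remove the bias only so far as they explain who was tested.

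**Working it through.** The plan states no figure for this point, so there is none to reproduce. The calculation is illustrative and asks what unequal testing alone would produce.

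**From the article**
- Recruitment target 800 and HIV prevalence 40% (Sample sizes, Observational study): 0.40 × 800 = 320 HIV-positive and 480 HIV-negative.
- Up to 200 children with SAM in the immunology substudy. At the same prevalence: 80 v 120.

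**Assumed, because the article does not give them**
- t, share tested: 80% v 50%, and as a wider case 90% v 30%.
- p, positivity among tested children: 10-20%, equal in both groups.
- c, share meeting clinical criteria: 20-30%, equal in both groups.
- A child is a case if either component is positive, and the two components are independent.

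**Formula.** Apparent rate = 1 − (1 − c)(1 − p·t).

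**Worked case**, c = 20%, p = 15%, tested 80% v 50%:
- More-tested group: 1 − 0.80 × (1 − 0.12) = 0.296.
- Less-tested group: 1 − 0.80 × (1 − 0.075) = 0.260.
- Odds ratio: (0.296/0.704) / (0.260/0.740) = 1.20.
- Two-sided 5% Wald test at 320 v 480: standard error √(0.296×0.704/320 + 0.260×0.740/480) = 0.0324, z = 0.036/0.0324 = 1.11, so about 20% of studies would be significant. At 80 v 120, z = 0.55 and about 9% would be.

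**Range of apparent odds ratios with no true difference**

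| c | p | 80% v 50% tested | 90% v 30% tested |
|---|---|---|---|
| 20% | 10% | 1.14 | 1.29 |
| 20% | 15% | 1.20 | 1.44 |
| 20% | 20% | 1.26 | 1.59 |
| 30% | 10% | 1.10 | 1.21 |
| 30% | 15% | 1.15 | 1.31 |
| 30% | 20% | 1.19 | 1.43 |

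At 80% v 50%, the share of studies significant at two-sided 5% is about 9-30% with 320 v 480 children, and about 6-11% with 80 v 120.

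**What changes the answer**
- *Equal testing.* The two rates are identical and the odds ratio is 1.00 in every row.
- *Overlap.* Suppose 80% of test-positive children already meet clinical criteria. With c = 20% and p = 15%, the rates are 0.20 + 0.2×0.15×0.8 = 0.224 and 0.20 + 0.2×0.15×0.5 = 0.215. The odds ratio falls from 1.20 to (0.224/0.776) / (0.215/0.785) = 1.05.
- *Overruling.* Suppose instead that a negative test cancels a clinical diagnosis, and half of the tested clinical cases are negative. With c = 20%, the rates are 0.20 × (1 − 0.8×0.5) = 0.12 and 0.20 × (1 − 0.5×0.5) = 0.15. The odds ratio is (0.12/0.88) / (0.15/0.85) = 0.77, so the direction reverses.

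**The case against.** **Nothing in the article says that testing differs by HIV status or immune profile.** This stands. A reader might infer that more heavily tested children will appear more infected and that testing intensity therefore becomes an HIV or immune effect. The text supports only that this may happen.

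**Laboratory results alone look much worse, but the plan does not use them alone.** Counting untested children as negative, 15% positivity at 80% v 50% tested gives 12.0% v 7.5%, a ratio of 1.6. No such laboratory-only outcome is stated; clinical criteria are part of the definition. The combined outcome is the relevant one, and its distortion is smaller.

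**Independence overstates the bias.** If wards test the children who look ill, most positives may already be clinical cases. This stands, and the overlap example shows the shrinkage.

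**Adjudication is planned across sites.** It should make diagnoses more consistent between hospitals. It cannot supply a culture that was never taken.

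**The analyses are declared exploratory and the covariate list is open.** Both are true. Exploratory interpretation does not remove a systematic error, and an open list does not commit the analysis to hospital or testing.

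**Details belong in the full protocol or SAP.** How clinical and laboratory evidence combine, and how tests not done are coded, may well be set there, and their absence from an article is not held against it. The point rests on what the article does state: the components of the outcome and the named covariates. Wording a definition around available tests is also an honest description of an observational study that leaves care to ward teams.

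**Conclusion.** The concern holds as a possible bias of modest, unknown size. The stated outcome mixes evidence available for every child with evidence available only for tested children, and the named adjustments do not address who was tested. Under the assumed 80% v 50% testing and the either-component rule, the apparent odds ratio with no true difference is about 1.10-1.26. It reaches 1.21-1.59 only at 90% v 30%. It is 1.00 with equal testing, nearer 1 with overlap, and could fall below 1 if negative tests overrule clinical diagnoses.

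It would be wrong to infer that the whole HIV comparison is compromised. In-hospital bacterial infection is one part of morbidity; all-cause mortality, relapse and anthropometry do not depend on these tests. The substudy's power statement concerns infectious mortality, and the article plans to adjudicate causes of death.

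**What to change.** 1. From existing records, flag for each child whether blood culture, stool culture and urinalysis were done, so that not tested is kept apart from tested negative.
2. Keep the combined outcome and, alongside it, analyse infection by the clinical criteria applied to all children.
3. Analyse laboratory-confirmed infection separately among tested children, weighted or adjusted for being tested (HIV status, severity, hospital).
4. Add hospital to the immunology regression models.
5. Report the proportion tested by HIV group, immune profile and hospital, so that readers can judge how far the combined result could be distorted.

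The cost is some extraction from records and a little more analysis, with no new procedures for participants. The clinical-only definition is less specific. That is why it should stand beside the combined outcome and not replace it.

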## Sample sizes

### Observational study

The observational cohort will recruit as many children with SAM as possible during the period of enrolment (July 2016 to March 2018), estimated at 600–800 children (capped at 800 maximum), to assess clinical and nutritional outcomes among HIV-positive and HIV-negative children hospitalised with SAM. Assuming mortality of 15%, overall loss to follow-up of 15% and recruitment target of 800 children, there would be 560 evaluable children at 48 weeks, of whom 224 would have HIV-SAM based on an estimated inpatient HIV prevalence of 40%. This will provide >80% power to detect absolute differences of 17% in binary outcomes between HIV-SAM and HIV-negative children with SAM, and of 0.33 times the SD in continuous outcomes.

